#### Study Visit 5 at 9 months following enrolment (allowable 44 days before or 45 days after scheduled visit):

Subjects that received either cefixime or BPG will be asked questions regarding their current symptoms, interval sexual history, concomitant antibiotic use and possible adverse reactions. Subjects will have a venipuncture blood specimen collected for syphilis testing (RPR). All participants will undergo pregnancy testing. Those that are found positive on pregnancy testing will be treated for syphilis according to national guidelines.

**Note:** A repeat venipuncture for serum collection at specimen collection follow-up visits (enrolment, 3, 6, and 9 months) will be performed if the initial specimen is determined to be inadequate following on-site centrifuge. Centrifuge and evaluation of specimen adequacy will be performed within 30 min of specimen collection. It is expected that repeat collection will rarely be needed as trained venipuncture staff will be responsible for collecting specimens. However, hemolysis can occur regardless of the venipuncture technique and this can contaminate the RPR assay and results.

**Reimbursement to subjects:** Study subjects, and their sexual partners who are referred to the study clinics for evaluation and treatment, will be reimbursed for their time and effort to participate in the study per local ethical authority guidelines.

**Partner referral and treatment:** All subjects will be encouraged to refer all partners with whom they have had vaginal, oral, or anal sex in the past 60 days to the clinic for routine evaluation and treatment. Upon presentation to the clinic, all partners will be tested and if positive, offered treatment according to local clinic guidelines.

### Discontinuation of study enrolment

Patients found to be pregnant at follow up visits will be removed from the study and given treatment with BPG based on stage and national guidelines. Patients that originally received one penicillin injection will receive treatment based on national guidelines.Women reporting a toxicity of grade 3 or greater, that are definitely or probably related to the study drug cefixime (to be determined by a physician not associated with the study), during the treatment period will be removed from the study.

### Main variables

Variables collected at time of enrolment will include age, past history of syphilis, RPR titer and HIV status.

The primary variables for outcome analysis will include:
The change in RPR titer between the baseline visit and by six months post enrolment.Safety and tolerability of study drug.

### Outcome measures

#### Primary outcome measure

The primary study outcome will be based on the change in the RPR titer from baseline to six months. Those subjects who have a 4-fold decrease in RPR titers from baseline by six months will be considered a positive treatment response (treatment success). All other participant outcomes will be defined as treatment failure including those subjects who experienced a fourfold (two titer) increase in RPR titer at three or six months post treatment and received BPG 2.4 million units IM once per week for 3 weeks.

**Note:** Subjects that received either cefixime or BPG that experience a 4-fold titer decline by three or months followed by a 4-fold titer rise by six or nine months will be classified as (1) treatment success at three months and (2) syphilis re-infection during the period following the initial 4-fold RPR titer decline.

**Note:** While there are limited data on the use of cefixime for the treatment of syphilis, cefixime is a broad spectrum, third generation cephalosporin in the same class and family as ceftriaxone for which extensive data on treatment efficacy for syphilis are available. RPR titers will be monitored frequently in this study and treatment with BPG will be provided if RPR titer increases fourfold (2 titer) at 3 or 6 months or does not reflect an adequate response (fourfold or 2-titer decline) at 6 months.

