**Fig. 1 Fig1:**
[figure not shown]
Standard care for syphilis diagnosis and treatment as per the Brazil Ministry of Health guidelines [34]. *NTT: Non treponemal test such as VDRL or RPR

Patients that are not eligible for the study (negative RPR or RPR with titer < 1:16) will receive syphilis RPR results and treatment according to national syphilis treatment recommendations from a study nurse. Pregnancy tests and HIV tests will be completed on all potential participants and those that test positive will not be enrolled in the study.

To benchmark the performance of BPG in the study population randomized to receive cefixime, a contemporary arm of participants that will receive standard of care treatment with BPG according to the Brazil national STI treatment guidelines will be included. A ratio of two patients receiving cefixime to one patient receiving BPG will be used.

This non-comparator arm of BPG will be included to account for study population differences in terms of stage of disease, history of prior infection, experience of re-infection, experience of serofast state, or other co-factors that could impact serological response. An estimate of performance of this standard of care will be calculated, but this will not be compared directly to the study intervention as the study is not powered to assess statistical significance between these groups.

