#### Study Visit 4 at six months following enrolment (allowable 44 days before or 45 days after scheduled visit):

Subjects that received either cefixime or BPG will be asked questions regarding their current symptoms, interval sexual history, concomitant antibiotic use and possible adverse reactions if they received cefixime. Subjects will have a venipuncture blood specimen collected for syphilis testing (RPR) increase in RPR titer at 3 or 6 months post treatment. Those subjects who experience a fourfold (two titer) increase in RPR titer at three or six months post treatment will be considered a treatment failure and will receive BPG 2.4 million units IM once per week three weeks. Data for these patients through Study Visit 4 will be included in analyses, and for analysis purposes, these patients will be considered to be treatment failures. All participants will undergo pregnancy testing. Those that are found positive on pregnancy testing will be treated for syphilis according to national guidelines and removed from the study. A voluntary repeat HIV test will be performed at 6 months. Patients that test positive for HIV at 6 months will be referred for HIV care. No additional treatment for syphilis will be provided based on HIV-positive status other than according to the study protocol. Response to treatment of these patients will be included in the analysis. Subjects that received either cefixime or BPG will be asked to return at 9 months from the time of treatment.

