### Study outcomes evaluation

#### Primary analysis

The primary outcome is the proportion cured using cefixime treatment, evaluated at six months post-recruitment.

Proportion representing proportion cured using cefixime treatment success, cure defined as at least 4-fold reduction in RPR titer by six months (compared to baseline). Participants experience a 4-fold reduction in RPR before six months will be counted as a success at six months.

The primary analysis will assess whether the proportion cured is greater than or equal to 90% and whether the observed efficacy is statistically different than the minimally acceptable efficacy set at 80%. Proportion cured and 95% confidence intervals will be calculated using the binomial exact test. Cefixime will be declared efficacious if the lower limit for a two-sided 95% confidence interval (CI)≥ 0.80.
*Cure:* At least a 4-fold decrease in RPR from baseline to 6 months.*Failure:* Less than a 4-fold decrease in RPR titer from baseline to 6 months, or an increase in RPR titer.*Non-evaluable:* At least one of the following: Subject did not return for 6 month visit, or RPR results from the 6 month visit were not available for any reason, or subject could not be evaluated for any other reason.

For the PP analysis population, subjects with non-evaluable outcome status will be excluded from the analysis. For the ITT analysis population, subjects with non-evaluable outcome status will be included in analyses and classified as treatment failures. Subjects who discontinued early from the study due to a lack of treatment effect are included in all analysis populations as treatment failures.

The primary efficacy analysis will be based on the cure rate by 6 months and will be performed in the PP analysis population. The primary analysis will also be performed in the ITT population, but this is a secondary outcome measure.

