### Ethical concerns

#### Potential risks

Potential risks to study participants include the possibility that the alternative treatment may not prove to be effective. For this reason, we will closely follow the subjects for adherence to study medication including daily phone or in-person contact to establish adherence to study drug. RPR titers will be collected 12 weeks after completion of treatment (with no more than 5-day result turnaround time). If the participant experiences an RPR titer increase of 4- fold or more from the entry RPR at 3 or 6 months, we will consider this a treatment failure and the participant and be given 2.4 million units of BPG immediately and according to national guidelines.Risks to privacy: Participants’ attendance at study visits may be accidentally noticed by others.Psychological risks: Receiving a positive syphilis diagnosis could be upsetting to a participant. However, syphilis diagnosis occurs as part of standard clinical care and outside of the study.*Risks associated with blood draw*: Participants may experience discomfort, bruising, or even fainting in connection with the blood draw that will be performed during the visits. There is also a slight risk of infection.Cefixime is contraindicated in patients with known allergy to cefixime or other cephalosporins. Some participants may not be aware of their allergy status. However, anaphylactic or anaphylactoid reactions (including shock and fatalities) have rarely been reported with the use of cefixime, thus this risk is considered to be very low.Some adverse reactions were documented in other cefixime clinical trials. In United States (U.S.) trials of the tablet formulation of cefixime, the most commonly seen adverse reactions were gastrointestinal events. These events were reported among 30% of adult patients that received either the twice daily or the once daily regimen. Discontinuation of cefixime during the U.S. clinical trials occurred among 5% of study participants because of drug-related adverse reactions. Other individual adverse reactions reported from U.S. clinical trials included diarrhea (16%), nausea (7%), loose or frequent stools (6%), flatulence (4%), abdominal pain (3%), and dyspepsia (3%). Observed and reported adverse reactions for cephalosporins including but not limited to cefixime have included allergic reactions, superinfection, renal dysfunction, toxic nephropathy, hepatic dysfunction including cholestasis, aplastic anemia, hemolytic anemia, hemorrhage, and colitis.In this study, participants will be observed for 30 minutes in the clinic following the first dose of cefixime. In the event of an adverse event or an allergic reaction possibly related to cefixime, participants will be evaluated by a study nurse and by a clinic-based study physician. Participants will be referred to emergency services at the discretion of the clinic-based study physician. Cefixime will be discontinued in the event of an allergic reaction.The efficacy of cefixime to prevent mother-to-child transmission of syphilis is unknown. Study participants will be counseled regarding the risk of untreated syphilis in pregnancy. Each participant will be offered oral contraceptive tablets as well as condoms to prevent pregnancy for the duration of the study. Condoms will be provided to each participant and use will be encouraged at each visit to reduce the risk of re-infection with syphilis and infection with other STIs.

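### A fourfold RPR rise after an initial fourfold fall is labelled re-infection from titer alone; for rises first seen at month 9 this is the only stated rule, so late relapse would be reported as new infection

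*Protocol article*

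**What the plan says.** All references are to the protocol article.

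- **Primary outcome measure, first Note.** In both arms, a fourfold decline followed by a fourfold rise by six or nine months is classed as a success at three months and then as "2) syphilis re-infection during the period following the initial 4-fold RPR titer decline". No exposure, partner or other evidence is required. One word has dropped out of the sentence where it gives the time of the decline; this does not alter the point.
- **Primary analysis.** Failure is "Less than a 4-fold decrease in RPR titer from baseline to 6 months, or an increase in RPR titer". The same section also says: "Participants experience a 4-fold reduction in RPR before six months will be counted as a success at six months".
- **Primary outcome measure, second Note.** "treatment with BPG will be provided if RPR titer increases fourfold (2 titer) at 3 or 6 months". The sentence goes on to give BPG also to women without a fourfold decline at 6 months.
- **Study Visit 4.** A "fourfold (two titer) increase in RPR titer at three or six months post treatment will be considered a treatment failure". Neither this section nor Primary outcome measure names the titer from which the increase is measured.
- **Potential risks.** This section does name it: a rise of "fold or more from the entry RPR at 3 or 6 months, we will consider this a treatment failure".
- **Study Visit 5 (9 months).** Women are asked about "interval sexual history, concomitant antibiotic use and possible adverse reactions. Subjects will have a venipuncture blood specimen collected for syphilis testing (RPR"). The section gives no rule for classifying a rise.
- **Participant recruitment.** The BPG arm is there to account for population differences, including "history of prior infection, experience of re-infection, experience of serofast state".

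Relapse is mentioned only in the background on ceftriaxone, where a meta-analysis reported it separately from serofast state and treatment failure.

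**The concern.** A titer that falls and later rises can mean that the drug suppressed the infection without clearing it, or that the woman was exposed again. The titer does not say which. The Note settles the question in advance and always in one direction: the rise is put down to new exposure and never to the drug.

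This matters most at month 9, where nothing else in the article classifies a rise. The trial is meant to inform a later trial in pregnant women, as the section on the selection of cefixime says. For that purpose a response that does not last is different from a lasting response followed by new exposure. The raw titers and sexual history are kept, so no information is lost. What is at stake is how late rises are described in the results.

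**Working it through.** The plan gives no figure for rebounds, so the main check sets the rules side by side.

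**1. Rises first seen at month 9.** Take illustrative titers of 1:32 at entry, 1:8 at months 3 and 6, and 1:32 at month 9.
- Primary analysis: fourfold reduction by six months, so Cure. The month-9 value is not used.
- Fourfold-increase failure rule (Study Visits 3 and 4, Primary outcome measure, Potential risks): covers months 3 and 6 only.
- Rescue rule (second Note): covers months 3 and 6 only.
- Study Visit 5: titer and sexual history collected, no classification.
- First Note: success at three months, then re-infection.

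Only the first Note applies, and it gives one possible cause.

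**2. Rises by month 6.** Let *d* be the fall from entry to month 3 and *r* the rise from month 3 to month 6, both in twofold dilutions.
- First Note: *d* ≥ 2 and *r* ≥ 2.
- Primary analysis: Failure if *d* − *r* < 2; Cure if *d* − *r* ≥ 2.
- Potential risks, failure: *r* − *d* ≥ 2 (fourfold above entry).

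Patterns that meet the Note but stay below the Potential risks threshold, for falls of 4-, 8- and 16-fold:

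| Fall *d* | Rise *r* | Failure | Cure |
|---|---|---|---|
| 2 | 2, 3 | 2 | 0 |
| 3 | 2, 3, 4 | 3 | 0 |
| 4 | 2, 3, 4, 5 | 3 (*r* = 3, 4, 5) | 1 (*r* = 2) |
| Total | 9 patterns | 8 | 1 |

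The one Cure pattern is, for example, 1:64, 1:4, 1:16. All nine also count as success under the early-reduction sentence. These are counts of patterns, not of women, and the cut at a 16-fold fall is a choice: a 32-fold fall adds Cure patterns at *r* = 2 and 3, and a 64-fold fall at *r* = 2, 3 and 4.

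The sequence 1:32, 1:8, 1:32 (*d* = 2, *r* = 2) shows the overlap. It is Failure by the definition (0 < 2), success by the early-reduction sentence, re-infection by the Note, and is retreated under the second Note because there is no fourfold decline at month 6. If the unnamed reference titer in Study Visit 4 were the previous titer, all nine patterns would also meet the fourfold-increase failure rule. Month 9 would be unchanged.

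**3. How much a descriptive table could show.** The stated cefixime size of 107 reproduces: with at least 94 successes needed, the exact upper-tail error at 0.80 is 0.0233 and the power at 0.90 is 81.9%. Approximate numbers of initial responders, assuming each has a later titer:
- Cefixime: 107 × 0.90 = 96.3, or from enrolment 140 × 0.80 × 0.90 = 100.8.
- BPG: 70 × 0.80 = 56 retained; with an assumed response of 0.80 to 0.90, 44.8 to 50.4.

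With no rises among *n* responders, the exact two-sided 95% upper limit is 1 − 0.025^(1/*n*):
- Cefixime: 3.8% (*n* = 96) or 3.6% (*n* = 101).
- BPG: 7.9% (*n* = 45) to 7.1% (*n* = 50).

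Five rises in 96 would be 5.2% (Clopper-Pearson 1.7% to 11.7%). These figures describe the precision of the proposed table, not the size of any harm.

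**The case against.** The strongest reply is that no stated analysis uses the label. The primary endpoint is at six months, the secondary outcome is safety, and there is no re-infection endpoint or decision rule. This stands, and it limits the point to how late rises are described.

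The design also helps. The Note applies equally to both arms, so an excess of late rises on cefixime could be seen descriptively against BPG whatever they are called. Partner referral and condoms should reduce re-infection. This stands too, but neither tells relapse from re-infection within the cefixime arm, and the label still states a cause.

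A table with intervals and subgroups is commonly left to the statistical analysis plan, which is not shown. Its absence is therefore not the fault here; the fault is the wording of a rule that the article does fix.

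A reader might infer three stronger points that the article does not support:
- *That relapse has no category at all.* By month 6 the Failure definition covers most rebounds and the second Note retreats women without a fourfold decline. The gap is at month 9.
- *That the label inflates the six-month cure rate.* What could keep a month-6 rebound as a success is the early-reduction sentence. That is a separate question, and renaming the rise does not answer it.
- *That the plan calls these women cured and then re-infected.* The Note says success at three months, which is limited in time.

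**Conclusion.** The point holds in a limited form. From titer alone and in both arms, the first Note names re-infection as the cause of every fourfold rise after a fourfold decline. For rises first seen at month 9 it is the only stated rule, so following the article as written would report any late relapse as new infection. For rises by month 6 the Note is one of several overlapping rules, and only Potential risks names the entry titer as reference.

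The six-month efficacy decision does not depend on the label. How many women are affected cannot be estimated from the article. The conclusion rests on the text and on no assumed rate; the response and retention assumptions serve only to size the table. This is an inexpensive improvement, not a threat to the primary result.

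**What to change.** Reword item (2) of the first Note to: *relapse or re-infection (4-fold rise after an initial 4-fold decline)*. Report the number and proportion of initial responders with such a rise by month 9, among those with a later titer, descriptively by arm under that neutral name. This suits the stated purpose of the BPG arm and makes no formal comparison. Exact 95% intervals and a split by interval sexual history, which is already collected at months 3, 6 and 9, are optional.

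The cost is one reworded line and one descriptive table. Endpoint, sample size and visits do not change. The drawbacks are small counts, imperfect self-report of exposure, and a result that may look less favourable to cefixime. The change removes the causal label; it does not decide which sentence of the Primary analysis governs a rebound at month 6.

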#### Secondary outcome measure

The secondary outcome measure is the safety and tolerability of cefixime as a treatment for syphilis.

This will be measured by the percent of treated patients experiencing mild, moderate, severe, or life-threatening adverse events, either temporally associated or not associated with the study product. Patients will be instructed on the possible side effects of the study drug, and when to call the study team should they experience any of these side effects. We will use the Common Terminology Criteria for Adverse Events (CTCAE) [35] to evaluate side effects and the severity of grade (scale 1–4). Women reporting a toxicity of grade 3 or greater, that is or probably related to study drug (to be determined by a physician not associated with the study), during the treatment period will be asked to stop study treatment, return to the clinic, and they will be treated with 2.4 million units of BPG. Patients will be followed closely until the toxicity returns to a grade 2 or less.

### Sample size considerations

The primary analysis will compute the proportion of subjects with a 4-fold decrease (from study entry RPR) in RPR titers from baseline by six months in the per-protocol (PP) analysis population.

We have powered this study to detect a significant difference from a minimal accepted efficacy of standard treatment with benzathine penicillin (80%). This minimal efficacy was selected based on a multi-center clinical trial evaluating the efficacy of penicillin versus azithromycin [36].

A 90% response rate for cefixime was selected based on recent meta-analyses, a multi-center trial of ceftriaxone for treatment of syphilis [10, 11, 37, 38]. To calculate the number of subjects required to enroll to reach 94 evaluable subjects in the PP analysis population, the following assumptions are made:

Using a two-sided exact binomial test at α = 5%, a sample size of 107 achieves an 80% power to detect a minimum acceptable cefixime efficacy (p_0_) of 0.80, assuming the anticipated efficacy proportion (p) of 0.90. Assuming 20% dropout rate and other related factors, the final sample size for the cefixime arm is inflated to *N* = 140, with correspondingly 70 participants recruited in the BPG arm, in a ratio (cefixime to BPG) of 2:1 (Table 4).

**Table 4 Tab4:** Sample size to detect a minimum acceptable efficacy (p_0_) of 0.80 using a two-sided Exact binomial test for difference assuming alpha = 5% and power = 80%*

Anticipated efficacy *P*	Sample size *	Effective sample size (20% inflated) *n*
0.86	316	395
0.87	225	282
0.88	173	217
0.89	131	164
0.90	107	**134**
0.91	88	110
0.92	69	87
0.93	55	69
0.94	48	60
0.95	41	52
0.96	34	43
0.97	26	33
0.98	26	33
0.99	17	22

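### The sample-size section names 94 evaluable per-protocol women as its target but derives 107; only 107 gives the stated 80% power

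*Protocol article*

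**What the plan says.** All the sample-size figures stand in the protocol article under Sample size considerations.

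- The lead-in sets the purpose of the calculation: "To calculate the number of subjects required to enroll to reach 94 evaluable subjects in the PP analysis population".
- The test is given as "Using a two-sided exact binomial test at α = 5" percent, and the result is that "a sample size of 107 achieves an 80% power to detect a minimum acceptable cefixime efficacy" of 0.80, "assuming the anticipated efficacy proportion (p) of 0.90".
- The title of Table 4 repeats the null value and the test: "Sample size to detect a minimum acceptable efficacy (p_0_) of 0.80 using a two-sided Exact binomial test". Its 0.90 row gives 107, and 134 after inflation.
- The enrolled number follows: "Assuming 20% dropout rate and other related factors, the final sample size for the cefixime arm is inflated to" 140, with 70 in the penicillin arm.

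The Primary analysis section fixes the population and the decision rule: "The primary efficacy analysis will be based on the cure rate by 6 months and will be performed in the PP analysis population", and "Cefixime will be declared efficacious if the lower limit for a two-sided 95% confidence interval (CI)≥ 0.80".

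**The concern.** Both 94 and 107 are offered as the number of evaluable cefixime women for one and the same test. The lead-in says outright that 94 is the per-protocol target. The next paragraph attaches the 80% power claim to 107. The figure 94 appears nowhere else in the article and is not derived.

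The evaluable per-protocol count is what a reader compares with the plan to judge whether the primary test was adequately sized. Anyone who takes the sentence naming that target at face value would regard 94 as enough for 80% power. A reader can find out which figure carries the power claim only by redoing the calculation.

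**Working it through.** **Inputs.** Null proportion p0 = 0.80, anticipated proportion p = 0.90, two-sided exact test at 5%, power 80% and dropout 20% come from Sample size considerations and Table 4. The success rule, an exact two-sided 95% lower limit of at least 0.80, comes from Primary analysis.

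**Method.** For each n, the critical count r is the smallest r with P(X ≥ r | n, 0.80) ≤ 0.025. This is equivalent to the exact (Clopper-Pearson) lower limit being at least 0.80. Power is P(X ≥ r | n, 0.90).

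**Step 1: reproduce the plan's figure.**
- n = 107: r = 94, upper-tail probability under 0.80 is 0.0233, lower limit for 94/107 is 0.801, power is 0.819.
- No smaller n reaches 80%, so 107 is the smallest n that does.
- Inflation: 107 / (1 − 0.20) = 133.75, rounded up to 134, as in Table 4. The text then takes 140.
- All 14 sample sizes in Table 4 reproduce by the same rule, so the protocol's method is not in doubt.

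**Step 2: put 94 through the same rule.**
- n = 94: r = 83, upper-tail probability 0.0247, lower limit for 83/94 is 0.8003, power is 0.772.
- Shortfall against the claim: 80.0 − 77.2 = 2.8 points.
- From n = 94 to n = 106 power never reaches 80%. The highest value is 79.2% at n = 101.

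**Step 3: can 94 be reconciled with the rest of the section?**
- Inflation: 94 / 0.80 = 117.5, rounded up to 118, which is neither 134 nor 140.
- Reaching 94 from 140 means a loss of 1 − 94/140 = 32.9%, against the stated 20%. Reaching 107 from 140 means a loss of 1 − 107/140 = 23.6%, which fits 20% dropout plus some allowance for other factors.
- 94 is not a sample size in any row of Table 4.
- Two-sided normal approximations at 80% power give 108 (null and alternative variances), 98 (arcsine) or 118 (continuity-corrected), none of them 94.
- A one-sided 5% exact test would give 85.6% power at n = 94, but the protocol specifies a two-sided test and a two-sided 95% interval.

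**Step 4: a possible origin.** 94 is exactly the number of cures needed among 107 evaluable women. It may be the critical count written as a sample size, or a figure left from another version of the calculation. The article does not say which.

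**The case against.** The strongest reply is that nothing in the design depends on 94. It occurs once, in a lead-in clause. The derivation beside it, Table 4, the 140 cefixime participants and the total of 210 all follow from 107, and the decision rule applies at whatever number turns out to be evaluable. All of this stands, and it limits how serious the error is. It does not remove the contradiction: two incompatible figures remain for the primary test, and one of them is wrong.

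Two stronger readings are tempting, and the document does not support them.

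- **That the study team would stop retention work, or call the trial complete, at 94.** No section makes 94 a retention, completion or stopping criterion. Enrolment is set at 210, visits are scheduled to nine months for all, and reminder calls are planned without reference to any count.
- **That the trial is under-powered at its expected evaluable number.** A reader might compute 140 × 0.80 = 112 and note that exact power there is only 77.2% (99 cures needed), practically the same as at 94. But the plan never states 112 as an expected per-protocol count. It allows for dropout together with unspecified other factors, and the per-protocol definition also removes ineligible and non-compliant women. The dip at 112 reflects the saw-tooth that every exact binomial test shows: power is 84.3% at 113. If evaluable counts are assumed to follow Binomial(140, 0.8), power averages about 80.5%. The saw-tooth is a separate matter from the 94 versus 107 contradiction.

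**Conclusion.** The lead-in figure of 94 evaluable women is wrong as written. Under the protocol's own test and decision rule, and its assumed true cure proportion of 0.90, 107 evaluable women give 81.9% power and 94 give 77.2%. The figure 94 matches neither Table 4 nor the inflation to 134 and 140.

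The consequence is modest. The misstatement concerns the number by which the adequacy of the primary test will be judged, not recruitment, the test or the success threshold. It should be fixed, but it gives no ground for calling the enrolled design inadequate. The conclusion that 94 is the stray figure rests on 107 and the whole of Table 4 reproducing exactly. How 94 arose remains unknown.

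**What to change.** In Sample size considerations, change the lead-in so that the per-protocol target reads 107 evaluable subjects. If 94 was meant as the critical count, say instead that at least 94 cures among 107 evaluable women are needed for the exact 95% lower limit to reach 0.80.

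Optionally, add a sentence that exact power varies in a saw-tooth with the number evaluable, for example 77.2% at 112 and about 80.5% on average if evaluable counts are assumed Binomial(140, 0.8). It should not present 112 as the plan's own expectation.

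The cost is one corrected figure. Enrolment of 140 and 70, Table 4 and the decision rule stay as they are.
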